## Results

Enrollment for the study will start in April 2023. We plan to complete the post assessments of the last worker in April 2023. The results are expected to be available still in the first semester of 2023.

## Discussion

### Significance of the Study

Given the high prevalence of WMSDs and the associated economic and personal burden, preventive measures such as smart wear for monitoring and providing feedback are crucial. The smart wearables analyzed under this study aim to create awareness of WMSDs risk and empower the worker to reduce the associated risk and have a healthier work environment and higher quality of life. Investing in preventive measures is especially rewarding, since workers in countries and sectors where more preventive measures are in place are less likely to report MSD complaints [10]. Consequently, preventive measures result in an increase in economic benefits for the industries with greater production and worker adherence to these jobs.

The proposed study is, to our best knowledge, one of the first to use devices that provides real-time feedback to industrial workers about posture. This real-time feedback will include the body location at risk, which can lead to the correction of body biomechanics. Posture and movement monitoring technology can help detect and subsequently reduce the compensatory movement patterns, promoting a decrease in fatigue and musculoskeletal symptoms.

### Strengths and Limitations

This study is a single-case experimental design. This method design was primarily developed to assess individual behavior. Given the main goal is to develop and test smart wear for reducing fatigue and poor biomechanics, a single-subject approach seems adequate. This design enables the possibility of rapidly determining if the wearables are effective. Immediate changes can be observed firsthand, quickly, and in individual participants. Consequently, adjustments can be rapidly made, if necessary. Contrary to the single-subject approach, a large sample statistical approach will require weeks or months of participant testing, mean calculations, and statistical analyses before the effectiveness may be determined. Conceptually, the treatment condition must influence individual behavior and assure both research intra- and interparticipant replication. Therefore, an ABAB design will be executed, assuring both intra- and interparticipant intervention and control [38]. Graphical analysis of the variability of each outcome, in each of the repeated measures in time, will be performed to explore the possible indicators of fatigue when performing the selected activity.

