## Methods

### Design and Setting

A longitudinal single-subject experimental design following the ABAB sequence [19] will be developed in a manufacturing industry real context. In the ABAB design, first, a baseline is determined (A), then the intervention is introduced, with the use of the smart wear and real-time feedback to the worker for the first time (B). Next, the intervention is withdrawn, returning to the baseline condition (A). Finally, after baseline stability is reestablished, the intervention is presented (B) for the second time [1,2]. All 4 periods will end with an assessment of the selected outcomes. Figure 1 depicts the study flow. Generally, in this study design, the research is done very thoroughly on 3 to 5 subjects. The interest is always in the meticulous examination of each participant individually, not in the group's average performance. Multiple single-subject experimental studies also present the opportunity to consider not only the individual variables but also analyze the trial at the environmental level [19,20].

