### Participants, Eligibility, and Recruitment

This study will include 5 active workers from an industrial manufacturing setting of household appliances in the Region of Aveiro, Portugal. To be included, workers must be aged between 35 and 45 years and have a work experience with the tested workstation for at least 6 months. Exclusion criteria are (1) history of vestibular disorders, (2) neurological, respiratory disease, or spinal surgery, (3) structural spinal problems, (4) medication or a health condition affecting balance, and (5) regular treatments for a musculoskeletal condition.

The workers will be recruited by the occupational health department, which will provide the identification numbers of each selected worker as well as shoe and clothing sizes.

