### Study Procedure

A specific task representing a repetitive movement was chosen. The task consists of the vertical screw tightening of 5 screws in a standing position into a piece placed horizontally. A first assessment period will be executed to analyze baseline repetitive work (A) outcomes. Subsequently, the workers will use the smart wearables and be provided with real-time feedback for 4 weeks (B). A second assessment (assessment 2) will be performed to explore the efficacy of the system. Afterward, the workers will have a washout period of 4 weeks to reestablish baseline repetitive work condition (A), followed by assessment 3. Finally, a second 4-week period of intervention (B) and consequent assessment 4, will take place (Figure 1). Each assessment moment will be accomplished in 5 consecutive days, in 4 periods of the day, which includes measurements for each period of 5 cycles of the performed task in the first 10 minutes after starting the shift (to avoid the warm-up period), 10 minutes before the break time, 10 minutes after the break, and 10 minutes before the end of the day's shift. All tests will be performed guaranteeing that in the anterior 48-hour period each individual did not participate in strenuous physical activities, which may affect the selected outcomes.

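### The ABAB design as described gives control within each worker and replication between workers, but it does not assure the interparticipant control that the article claims

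*Protocol article*

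**What the plan says.** Under Strengths and Limitations, the article first names replication within and between participants as the aim. It then states that "an ABAB design will be executed, assuring both intra- and interparticipant intervention and control".

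The Methods describe the design as follows:

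- **Sequence** (Design and Setting): "A longitudinal single-subject experimental design following the ABAB sequence". No other order is mentioned, and each of the four periods ends with an assessment.
- **Setting** (Participants, Eligibility, and Recruitment): "This study will include 5 active workers from an industrial manufacturing setting of household appliances".
- **Baseline** (Study Procedure): "A first assessment period will be executed to analyze baseline repetitive work (A) outcomes". No length is given beyond the assessment days.
- **First intervention period** (Study Procedure): "the workers will use the smart wearables and be provided with real-time feedback for 4 weeks (B)".
- **Withdrawal** (Study Procedure): "Afterward, the workers will have a washout period of 4 weeks to reestablish baseline repetitive work condition (A), followed by assessment 3". A second 4-week intervention period and assessment 4 follow.

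Design and Setting words the start of the second B differently: it follows once the baseline has settled again, with no fixed time. The Data Analysis section plots and judges each worker separately. Nothing shown describes staggered or randomised start dates, or a comparison worker.

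**The concern.** Reversal lets a worker act as his or her own control. Control between workers needs something more: when one worker changes phase, others must be under observation and not changing phase, so that a shared cause can be told from the intervention. The article claims this property, but the design it describes has no feature that would supply it.

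The setting makes this relevant. The study runs on a working factory floor, and each worker's assessments are separated by weeks. A change in line speed, tooling, product mix or temperature between two assessments could move the outcomes of all five workers in the same direction. If their phase changes coincide, the five graphs agree on that contrast. A reader who relies on the claimed control would count five confirmations of what is, for a plant-level cause, a single event.

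**Working it through.** The plan gives no figure on this point, so the check lays out the schedule and follows a plant-level change through it.

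**Inputs.** Five workers; sequence ABAB; B, A and B of 4 weeks each; an assessment of 5 days at the end of each period (Study Procedure). Assumptions: each assessment takes one week, the three later ones follow their 4-week period, and a worker who has not yet started counts as being in A. The Abstract says the 5 days are nonconsecutive. If so, assessments take longer than a week and the week counts below lengthen.

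**Step 1: common start.** One block is 4 + 1 = 5 weeks, so assessments fall in weeks 1, 6, 11 and 16. Phase changes number 5 x 3 = 15, on 3 dates. In no week is one worker in A while another is in B.

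**Step 2: one lasting plant-level change of size d, common start.** Let e be the true intervention effect. The three contrasts in each worker are:

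| Source | B1 - A1 | A2 - B1 | B2 - A2 |
|---|---|---|---|
| Intervention only | e | -e | e |
| Change between A1 and B1 only | d | 0 | 0 |
| Change between B1 and A2 only | 0 | d | 0 |
| Change between A2 and B2 only | 0 | 0 | d |

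The change enters one of the three contrasts, and the same one in all five workers. It does not produce e, -e, e. A plant-level cause would have to switch on, off and on again in step with the phases to do that. Weeks 1 to 16 have 15 week boundaries, and a change at any of the 15 acts on the same contrast in every worker.

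**Step 3: workers started one week apart.** Worker k is assessed in weeks k, k+5, k+10 and k+15:

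| Assessment | Weeks, workers 1 to 5 |
|---|---|
| A1 | 1-5 |
| B1 | 6-10 |
| A2 | 11-15 |
| B2 | 16-20 |

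The 15 phase changes now fall on 15 dates. Weeks 1 to 20 have 19 boundaries. Of these, 4 x 4 = 16 lie inside an assessment block and 3 lie between blocks (5/6, 10/11, 15/16).

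- *Inside a block.* A change after week 2, for example, shifts B1 - A1 in workers 1 and 2, whose A1 came before it. It leaves workers 3 to 5 untouched, since all their assessments come after it. A change after week 7 shifts A2 - B1 in workers 1 and 2 but B1 - A1 in workers 3 to 5. Workers disagree, and a calendar axis shows why.
- *Between blocks.* A change between weeks 5 and 6 still lies between A1 and B1 for all five.

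**Step 4: what the stagger does not give.** By phase, workers in A and B coexist in weeks 2-5, 7-10 and 12-15, which is 12 of 20 weeks. By measurement, one worker is assessed per week and every A1 assessment precedes every B1 assessment. The number of weeks in which one worker is measured in A while another is measured in B is therefore 0.

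**The case against.** The strongest reply is that this is loose wording in a Discussion. The sentence follows from an aim stated as replication, and it can be read as saying only that every worker goes through both conditions. The analysis looks at each worker alone and never uses one as another's control. That reading is fair to the intent. It is still not interparticipant control, and the sentence says the design assures it.

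A reader might also infer several stronger points, which the documents do not support:

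- *That all five workers start on the same day.* The article does not say so. The collective wording of the Study Procedure is ordinary prose and the study flow figure is not available. The Results section says "We plan to complete the post assessments of the last worker in April 2023", with enrollment opening in the same month. That cannot establish a common start: the three 4-week periods alone take 12 weeks, so from 1 April 2023 they end on 24 June. A timetable that cannot hold one worker's sequence says nothing about how the workers are aligned. What stands is that nothing in the article assures different dates, and incidental differences in start would not assure them either.
- *That phase lengths are firmly fixed for everyone.* The 4 weeks are explicit for B, A and B, but the stability condition in Design and Setting is in tension with them.
- *That a plant-level change would appear as a replicated intervention effect.* The reversal guards against this. A single lasting change alters one contrast and leaves the full pattern unexplained.
- *That staggered starts would supply concurrent controls.* With outcomes measured only at the end of each period, they would not.

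**Conclusion.** The claim of assured interparticipant control is not supported by the design as described. Intraparticipant control by reversal is untouched, and agreement across five workers is legitimate replication.

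The point is small. It changes how agreement between workers on a single phase contrast may be read, not whether the study can be interpreted. Under a common start, a lasting plant-level change between any two assessments would affect the same one of three contrasts in all five workers. That start is a possibility the article leaves open, not a fact it states. The week counts also assume one-week assessments after each 4-week period and an abrupt change at a week boundary; gradual drift would be separated less cleanly.

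**What to change.** 1. In Strengths and Limitations, replace the claim with intraparticipant control and interparticipant replication.
2. Add there that plant-level changes coinciding with a phase change cannot be excluded.
3. Plot all five workers on a common calendar axis as well as by phase.
4. Reconcile the fixed 4-week withdrawal in Study Procedure with the stability condition in Design and Setting, so that it is clear what determines the start of the second B.

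These are text and plotting changes. They need no additional workers, visits or measurements.

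**Optional.** Start the workers one week apart, in an order drawn at random, with the period lengths left as they are. On the assumptions above, the study runs 20 calendar weeks instead of 16. The assessment equipment is in use in up to 20 weeks, against 4 with a common start, which must be weighed against the Introduction's wish to disturb production as little as possible. Motion Analysis describes one workstation being prepared with six cameras, so spreading workers over weeks may suit the logistics. The gain is that changes at 16 of 19 week boundaries no longer act on the same contrast in every worker; those at the other 3 still do. If this is adopted, the article should state that limit and should not present the stagger as concurrent control.

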### Conclusions

This proposed study will explore a strategy for reducing fatigue and musculoskeletal symptoms in industrial workers, possibly preventing WMSDs, using smart wearables that provide real-time feedback about biomechanics. Results would showcase a novel approach for improving postural awareness and self-awareness of risk for WMSD providing an evidence-based support for the use of such devices. Further research could explore other health indicators and individualized approaches to prevent similar health risks.

## Abbreviations

EMG: electromyography
GAD-7: General Anxiety Disorder 7-item scale
MSD: musculoskeletal disorder
PHQ-9: Patient Health Questionnaire-9
RAPA: Rapid Assessment of Physical Activity questionnaire
RPE: rating of perceived exertion
RULA: risk stratification of range of motion
WMSD: work-related musculoskeletal disorder
